Secondary outcomes: Other quantitative outcomes include pain, assessed using the nine-item KOOS-Pain questionnaire^15^ with a 5-point ordinal response scale, higher scores indicating higher levels of pain. Activity level will be assessed using the lower extremity activity scale,^17^ a single item self-reported question with 18 states of activity, higher numbers indicating higher level of activity. Quality of life will be assessed using the EuroQoL-5 Dimensions-5 Levels questionnaire,^18^ capturing five domains of health, namely mobility, self-care, usual activities, pain/discomfort and anxiety/depression. The overall score ranges from 0 to 1, higher score indicating better quality of life. Safety, knowledge about recovery, rehabilitation adherence, satisfaction with surgical outcome and cost incurred will be collected using study-specific questionnaires. Active and passive knee ROM^19^ of the operated knee(s) will be measured using a digital goniometer. Performance-based measurements include chair rising test to assess lower limb strength, stair climbing and 6 min walk tests to assess knee function, timed-up and go to assess gait stability,^20^ and single leg stance to assess balance.^21^ Further explanation of the measurement tools is found in table 2 and the standardised procedure to conduct the performance-based tests is illustrated in online supplemental efigure 8.

**Table 2 T2:** Trial outcomes and schedule of data collection

	Study period					
Time point	Enrolment	Baseline (0)		Visit 1 (3 months)		Visit 2 (6 months)
Screening	X		Telephonic health check-in		Telephonic health check-in	
Informed consent	X					
Health history (comorbidities)		X				
Randomisation	X					
Patient-reported outcome measures						
Knee function*		X		X		X
Knee pain†		X		X		X
Activity level‡		X		X		X
Quality of life§		X		X		X
Knee range of motion¶		X		X		X
Safety** (falls and rehospitalisation)				X		X
Knowledge about recovery††				X		
Rehabilitation adherence‡‡				X		
Cost incurred by patients§§				X		X
Satisfaction with surgical outcome¶¶						X
Performance based measures*** Function (SCT, 6MWT), Gait stability (TUG), Lower limb strength (CRT), Balance (SLS)				X		X
Process indicators††† Implementation fidelity and reach of the intervention, app usage, barriers and facilitators to implementation and end user satisfaction.						

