### Statistical methods

#### Statistical methods for primary and secondary outcomes

Effectiveness outcomes: Baseline characteristics including mean, SD, number and percentage will be described. Mean group differences and 95% CI of KOOS-ADL score at 3 and 6 months adjusted for baseline score will be calculated using mixed effect linear regression. A p value of 0.025 will be considered as statistically significant for each of the time points. The analytical approach will be modified intention-to-treat, which includes all those who were randomised irrespective of their adherence to trial protocol if they had at least one follow-up visit after enrolment. This approach will exclude those who were lost to follow-up after enrolment.

All secondary continuous outcomes that include KOOS-Pain, ROM and performance-based measures will be compared at 3 and 6 months using linear mixed effect method adjusted for baseline KOOS-ADL, as performance-based measures will not be collected at baseline. A statistical analysis plan will be developed before the end of trial recruitment and made publicly available before final analysis. No interim analysis will be performed. The preplanned subgroups are gender and laterality of index surgery (bilateral/unilateral). Effect modification will be claimed based on interaction p<0.05. We will not perform a per-protocol analysis. Multiple imputation of missing primary outcome will be done only if more than 5% of enrolled are lost to follow-up. All analyses will be done in Stata (StataCorp) and R version 4.4.1 or higher (Postit Team, 2025).

Process evaluation: App usage (usage of diary, type of exercise prescribed and number of times therapy was modified) will be presented graphically along with suitable summary measures. The written research coordinators’ notes will be quantified using a fidelity checklist. Transcripts of qualitative interviews will be coded independently in NVivo software (Lumivero (2023) NVivo (V.14)), using an inductive-deductive approach followed by thematic analysis. The qualitative findings from the interviews, fidelity checklist, rehabilitation adherence and knowledge score, and functional outcomes will be triangulated to understand the mechanistic pathway to change, whether intervention use/non-use led to different outcomes. Further, contextual factors affecting the implementation and usage of the intervention will be summarised.

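### KOOS-Pain, ROM and lower extremity activity are to be adjusted for baseline KOOS-ADL although their own baselines are collected, which may lose precision

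*Protocol article*

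**What the plan says.** The section on statistical methods for primary and secondary outcomes sets one rule for the secondary analyses: "All secondary continuous outcomes that include KOOS-Pain, ROM and performance-based measures will be compared at 3 and 6 months". The covariate and its justification follow in the same sentence: "using linear mixed effect method adjusted for baseline KOOS-ADL, as performance-based measures will not be collected at baseline".

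The primary outcome is treated differently, since it is adjusted for its own starting value: "KOOS-ADL score at 3 and 6 months adjusted for baseline score will be calculated using mixed effect linear regression".

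Table 2 in the Outcomes section shows which baselines exist. Each of these rows is marked at baseline, 3 months and 6 months:
- range of motion: "Knee range of motion¶ X X X"
- activity level: "Activity level‡ X X X"
- quality of life: "Quality of life§ X X X"
- knee pain, with the same three marks

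The performance-based measures are marked only at 3 and 6 months.

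**The concern.** The only reason given for using KOOS-ADL, "as performance-based measures will not be collected at baseline", is true of the stair climb, walk, timed-up-and-go, chair-rise and single-leg-stance tests. It is not true of KOOS-Pain or ROM, which the same sentence names. It is also not true of lower extremity activity, which falls under the rule if its 18-level scale is analysed as continuous. For these outcomes a substitute covariate replaces a measurement that the trial already takes.

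A follow-up value is usually best predicted by its own earlier value. Where that holds, the substitute leaves more residual variance, widens the interval for the group difference, and corrects a chance imbalance in baseline pain or motion only as far as KOOS-ADL tracks it. Pain and lower limb activity are part of the superiority hypothesis in the Introduction, and pain, ROM and activity are key secondary objectives.

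This is not a detail left to the statistical analysis plan. The protocol states the covariate, so a later plan either inherits it or has to justify a departure.

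**Working it through.** **1. Does the stated reason cover the outcomes it is applied to?**

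| Outcome | Baseline in Table 2 | Planned covariate | Does the reason apply? |
|---|---|---|---|
| KOOS-ADL (primary) | yes | own baseline | not needed |
| KOOS-Pain | yes | baseline KOOS-ADL | no |
| ROM | yes | baseline KOOS-ADL | no |
| Lower extremity activity | yes | baseline KOOS-ADL, if treated as continuous | no |
| Performance tests | no | baseline KOOS-ADL | yes |

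**2. The plan's own figure.** The article states no precision for secondary outcomes. Its sample size gives the number of completers. Taking the Sample size section's inputs as stated (effect size 0.40, 85% power, two-sided 0.025 per time point, 10% loss):

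n = 2 × (2.241 + 1.036)² / 0.40² = 134.3, so 135 per arm; 135 / 0.90 = 150.

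This reproduces the stated figure of about 150 per group. It concerns the primary outcome and is unaffected by this point.

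**3. Precision under the two covariates.** At a given time point, the variance of the adjusted group difference is proportional to 1 − r², where r is the correlation of the follow-up value with the covariate used. Therefore

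variance ratio (KOOS-ADL versus own baseline) = (1 − r_ADL²) / (1 − r_own²),

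and the interval-width ratio is its square root. The documents give neither correlation. The assumed ranges are r_own 0.3 to 0.6 and r_ADL 0.1 to 0.3.

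| r_own | r_ADL | Variance ratio | Width ratio | Equivalent completers per arm (of 135) |
|---|---|---|---|---|
| 0.3 | 0.3 | 0.91/0.91 = 1.00 | 1.00 | 135 |
| 0.3 | 0.1 | 0.99/0.91 = 1.09 | 1.04 | 125 |
| 0.4 | 0.2 | 0.96/0.84 = 1.14 | 1.07 | 119 |
| 0.5 | 0.3 | 0.91/0.75 = 1.21 | 1.10 | 112 |
| 0.6 | 0.3 | 0.91/0.64 = 1.42 | 1.19 | 95 |
| 0.6 | 0.1 | 0.99/0.64 = 1.55 | 1.24 | 88 |

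The range is 0% to 55% for variance and 0% to 24% for interval width. In the 0.5/0.3 case the loss equals 1 − 0.75/0.91 = 18% of the completers for that outcome. In the same case, with 135 per arm, a true effect of 0.30 SD and a two-sided 0.05 test (both assumed for illustration), power is 81% with the own baseline and 73% with KOOS-ADL.

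**4. Both covariates together.** A linear model with both covariates explains at least as much variance as either alone. Its price is one degree of freedom out of about 270 completers, which is negligible. The combined model therefore loses essentially nothing even where the own baseline turns out to be the weaker predictor.

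**The case against.** The case against is mainly about size and reach, and much of it stands.

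- **The loss may be nil.** Within the assumed ranges, equal correlations give a ratio of 1.00. KOOS-Pain and KOOS-ADL are subscales of one questionnaire, so their baselines may carry much the same information. A reader might infer that a loss is certain; the documents give no correlation that would show this.
- **For ROM the own baseline may be a mixture.** The eligibility section allows screening up to hospital discharge after the operation, and baseline data precede randomisation. Some goniometry may therefore be postoperative, whereas baseline KOOS-ADL is defined as the status before surgery. This is a fair reason not to rely on raw baseline ROM alone. It is no reason to leave it out, and it does not touch KOOS-Pain.
- **The analysis is valid as planned.** A reader might infer bias, or that imbalance goes wholly uncorrected. Neither follows: randomisation protects the comparison in expectation, and a correlated covariate corrects part of any chance imbalance.
- **The reach is limited.** The rule covers continuous secondary outcomes, so falls and readmissions are outside it. EQ-5D-5L utilities have a separate bootstrapped comparison in the cost analysis. A reader might also suppose that the cost ratio per 5° of flexion inherits the weaker adjustment, but the cost section does not say which model supplies the flexion difference.
- **The analysis plan could still change it.** True, but that would be a departure from a stated choice.

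None of this supplies a reason for applying a rule justified by missing baselines to outcomes whose baselines are present.

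**Conclusion.** The point holds in limited form. The stated justification does not apply to KOOS-Pain, ROM or lower extremity activity, and the plan passes over baselines it collects. The consequence is a possible loss of efficiency, and only partial correction of chance imbalance, in secondary comparisons. It is not bias, and the primary analysis, its error rate and the sample size are untouched. The size rests wholly on assumed correlations: anywhere from no loss to 55% more variance, with 21% more variance and 10% wider intervals at 0.5 and 0.3. It is likely to differ by outcome and may be small for KOOS-Pain. The change is still worth making, because a model with both baselines gives up essentially no precision whichever covariate proves the better predictor.

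**What to change.** Amend the sentence in the statistical methods, and carry it into the statistical analysis plan, as follows:

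- KOOS-Pain, ROM and lower extremity activity: adjust for the outcome's own baseline value, optionally with baseline KOOS-ADL as a second covariate.
- Performance-based tests: keep baseline KOOS-ADL alone, as now.
- ROM: because enrolment may fall before or after surgery, add an indicator of whether baseline ROM was taken before or after the operation, and its interaction with baseline ROM. The indicator alone shifts the mean but would force the same slope on both kinds of baseline.
- EQ-5D-5L: if it is also analysed under this rule, treat it in the same way as KOOS-Pain.

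The cost is a few lines of text. No further patients or visits are needed, and the baseline values are already scheduled; the timing indicator follows from the dates of baseline assessment and surgery. The article says the analysis plan will be written before recruitment ends and published before the final analysis, so the change can be made and explained there.

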### Outcomes

Primary outcome: Early recovery of knee function is one of the desired outcomes by patients undergoing knee arthroplasty.^14^ The primary outcome knee function will be assessed using the ADL subdomain of Knee Injury and Osteoarthritis Outcome Score (KOOS). It is a validated tool to evaluate post knee rehabilitation interventions^15^ and will be completed by the trial participants at baseline (before surgery status), 3 and 6 months after surgery in both groups. The total score ranges between 0 and 100 and the minimum clinically important group difference for this domain ranges from −1.5 to 15.5 units.^16^ The KOOS-ADL questionnaire will be self-administered in paper during the follow-up visit by the patient. If the patient is not able to complete it by self, then the family member will assist in eliciting the responses from the patient. In the absence of a family member, an independent assessor, not involved in the intervention implementation and rehabilitation, will administer the questionnaire. The primary comparisons would be to compare the end value of KOOS-ADL score at 3 and 6 months independently between the two groups adjusted for baseline score.

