### Sample size

The primary endpoints are group differences in self-reported knee function measured using the KOOS-ADL at 3 and 6 months using mixed-effect linear regression. The KOOS-ADL score ranges from 0 to 100 with higher scores indicating better function. We aim to detect a difference of at least 7 points,^16^ and a common SD of 15 points was assumed. The sample size was estimated assuming two-sided, two-sample equal-variance t-test, with an overall type I error rate (α) of 0.05. The effect size is defined as d=(μ1−μ2)/σ, where σ is the common SD for both groups. To detect a population effect size of 0.40 with 85% marginal power, the number of needed participants will be around 150 in each group after adjusting for 10% loss to follow-up and multiplicity due to two primary time points using Bonferroni’s correction. The sample size was computed using PASS 2023, V.23.0.2. We expect to reach the target sample size in 18 months.

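### Effect modification by gender or laterality is to be claimed at an uncorrected interaction p<0.05, with no exploratory label; the chance of a false claim is about 10% to 18.5%, depending on a test count the protocol does not give

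*Protocol article*

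**What the plan says.** All of the subgroup text is in the protocol article, under Statistical methods for primary and secondary outcomes. The factors are given as: "The preplanned subgroups are gender and laterality of index surgery (bilateral/unilateral"). The decision rule follows directly: "Effect modification will be claimed based on interaction p<0.05". Nothing there labels the subgroup analyses exploratory, limits them to particular outcomes or visits, or adjusts for how many are done.

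The same section treats the main effect on KOOS-ADL more strictly: "A p value of 0.025 will be considered as statistically significant for each of the time points". The reason is in the Outcomes section, where the 3- and 6-month comparisons are separate: "The primary comparisons would be to compare the end value of KOOS-ADL score at 3 and 6 months independently between the two groups". The Sample size section carries the same correction through to the target of "150 in each group after adjusting for 10% loss to follow-up and multiplicity due to two primary time points using Bonferroni’s correction".

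The article also says that a statistical analysis plan will be written before recruitment ends and published before the final analysis. That plan is not at hand.

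**The concern.** The sentence does more than describe an analysis. It commits the trial to a conclusion whenever an interaction p value falls below 0.05. There are at least two such tests, and possibly four on the primary outcome alone. The plan accepts that two time points call for a correction of the main effect, but applies none to the subgroup tests. If those tests are done at each visit, a subgroup claim faces a looser threshold (0.05) than the treatment effect at the same visit (0.025), and no reason is given.

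At stake is what the trial may say about its subgroups. Under the rule as written, a chance result would be reported as a finding that the app works differently in men and women, or after unilateral and bilateral surgery.

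**Working it through.** **Reproducing the plan's own figure.** The Sample size section states a standardised effect of 0.40, 85% power, two-sided testing and Bonferroni over two time points (0.05/2 = 0.025 each).
- n per group = 2 × (z for 0.025 two-sided + z for 85% power)² / 0.40² = 2 × (2.241 + 1.036)² / 0.16, which rounds up to 135.
- With 10% loss: 135 / 0.90 = 150. This matches the stated figure and confirms that the main effect is tested at 0.025 per time point. The plan gives no corresponding error rate for the subgroup tests.

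**Chance of at least one false interaction claim on KOOS-ADL, with no true effect modification.**

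Inputs from the protocol: threshold 0.05 per test; two factors; two primary time points. Assumptions not in the protocol: whether interactions are tested at one or both visits; the correlation r between the 3- and 6-month interaction statistics; independence of the two factors.

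*Case A, each factor tested once (two tests).* 1 − 0.95² = 0.0975, about 1 in 10.

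*Case B, each factor tested at both visits (four tests).* Let q(r) be the chance that at least one of a factor's two correlated statistics exceeds 1.96 in absolute value, from the bivariate normal distribution. Over both factors the rate is 1 − (1 − q)².

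| r | q per factor | Rate over both factors |
|---|---|---|
| 0 | 0.0975 | 0.1855 |
| 0.5 | 0.0907 | 0.173 |
| 0.7 | 0.0835 | 0.160 |
| 0.9 | 0.0704 | 0.136 |

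If the statistics for the two factors are themselves correlated (0.2 to 0.4), simulation gives 0.153 to 0.171 for r of 0.7 to 0.5, slightly below the independent case.

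**How much an interaction test could show.** Assume the stated SD of 15, 135 evaluable per arm and a 50/50 split of the factor (the split is not in the protocol).
- Each of the four cells has 67.5 participants, so the standard error of the interaction is 15 × √(4/67.5) = 3.65 points.
- To reach p<0.05, the estimated interaction must exceed 1.96 × 3.65 = 7.2 points, slightly more than the 7-point main effect the trial aims to detect.
- Power for a true 7-point interaction is about 48%, or about 42% with a 30/70 split.
- Adjustment for baseline KOOS-ADL would improve these figures by an amount the protocol does not allow one to calculate.

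**What a correction would do.** At 0.05/4 = 0.0125 per test, the four-test rate falls to 0.049 if independent and 0.047 at r = 0.5. On the 50/50 assumption, power for a 7-point interaction falls from about 48% to about 28% (7/3.65 = 1.92, against a critical value of 2.50).

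**The case against.** The case for leaving the text alone has real force. There are only two factors, both are named in advance, and the rule uses a formal interaction test with a preset threshold instead of comparing p values within subgroups. An unadjusted 0.05 for a few planned interactions is a common convention. No subgroup question appears among the objectives, and only the two primary comparisons are sized and protected. Outcomes, visits, exploratory status and multiplicity for subgroup tests are usually set out in the statistical analysis plan.

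Most of this stands and limits the weight of the point. It does not remove it, because the protocol has not left the matter open: it has already fixed the wording that a claim will be made at p<0.05, and a later plan that follows the protocol would inherit it.

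Stronger readings are tempting, and the document does not support them:
- A reader might infer a false-claim rate of roughly 1 in 6. That needs four tests and a between-visit correlation of about 0.5 to 0.7. The word *independently* in the Outcomes section describes the comparison between the two groups, not the subgroup tests, and no correlation is given.
- A reader might measure the rate against the overall 0.05 in the Sample size section. That 0.05 belongs to the primary comparisons; the protocol never places the interaction tests in that family and never calls them confirmatory.
- A reader might infer that a chance subgroup result would decide who is offered the app. The article speaks of refinement, stakeholder consultation and scalability, not of restricting the app by subgroup.

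**Conclusion.** The point holds as a minor one. The protocol states a rule for claiming effect modification that ignores the number of tests and carries no exploratory label, while the same section corrects the main effect for its two time points. With no true effect modification, the chance of at least one false claim on KOOS-ADL is about 10% with one test per factor, and about 14% to 18.5% with tests at both visits (between-visit correlation 0.9 to 0, factors independent). Which figure applies cannot be read from the text. The rule is also not expressly limited to the primary outcome, so the number of tests could be larger.

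The type I error of the primary comparison is unchanged, since the 0.025 threshold per time point does not depend on the subgroup rule. What changes is only what may be concluded about gender and laterality.

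**What to change.** Replace the claim sentence, in the statistical analysis plan and in any protocol update, with wording such as: *The subgroup analyses by gender and laterality are exploratory. Interaction estimates will be reported with 95% confidence intervals and p values, and no claim of effect modification will be made from p<0.05 alone.* Stating which outcomes and visits are covered would let readers count the tests.

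This needs no new data or participants. The downside is that a nominal interaction p<0.05 could no longer be announced as established effect modification.

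Keeping a claim rule at a corrected level such as 0.0125 is possible but is a debatable trade-off, given the loss of already limited power shown above. It is not needed to resolve the point.

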### Trial management

This is an investigator-initiated project with a low-risk intervention and no anticipated potential harm to participants, thus the trial will be overseen by the project coordination team with the principal investigator taking up the responsibility of trial oversight. Hence, a data safety monitoring committee was not appointed for this trial. The project coordination team consists of the trial manager, research coordinators and the principal investigator to provide oversight of the day-to-day management of the trial, review trial progress with recruitment, retention and data quality. Any protocol amendments related to patient eligibility criteria, increase in sample size, duration of trial participation and change in prespecified trial outcomes will be approved by the ethics committees before implementation and updated in the trial registry.

